### Aim Specific

We will use generalized linear models with repeated measures (GLMRM) for each aim where outcome variables may have different form (continuous, binary or count) and the measurements are likely to be correlated due to residing in the same building or being from the same participant over time. The models use various link functions to relate outcome to linear combination of predictors. For example, identity link for continuous outcome is linear model with repeated measures and logit link for binary outcome is logistic model with repeated measures. We will use the generalized estimation equation method to estimate model parameters and make statistical inference since it takes into account intra- cluster (within-building or within-person) correlations and uses all available data.

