### Trial design {8}

The trial design is a borough-stratified, four-arm, factorial-design, cluster RCT that targets 64 randomly selected buildings (16 buildings per arm) in separate NYCHA developments. We are recruiting and following 8 randomly selected residents stratified by smoking status − 4 smokers and 4 non-smokers - per building (n = 512) into four arms: (1) reduction/cessation, (2) resident endorsement, (3) reduction/cessation plus resident endorsement and (4) the standard approach (128 participants per arm) as shown in Fig. 1. A partnering community-based organization, Health People, Inc., specializing in peer-to-peer health education will train and supervise peer educators (PEs) who will then deliver the designated interventions. Quantitative assessments via survey questionnaire, salivary cotinine measurements, as well as sensory building observations will be used to measure outcomes. We will be evaluating the efficacy of compliance support interventions in reducing personal smoking and exposure to second-hand smoke in public housing. In addition, we will also determine if the tobacco retail environment surrounding a given public housing building moderates the relationship between compliance support interventions and smoking-related outcomes.

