#### Sample Size {14}

Power analysis was conducted using software PASS.15 for the primary outcome (change in salivary cotinine over a year) in Aims 1 and 2. Sampling 16 clusters (buildings) with 4 subjects per cluster (smokers for Aim 1, non-smokers for Aim 2) in each arm, we have 128 subjects per group or 256 in groups with or without a specific type of treatment (e.g. resident endorsement vs. no endorsement, cessation vs. no cessation). We calculated effect size as group mean difference in unit of standard deviation (SD) of the outcome, based on a two-sided test for mean difference between two groups in a cluster-randomized design with power of 80%. To compare groups with and without specific type of treatment, the group size of 256 may detect effect size of 0.283SD, 0.299SD, 0.312SD at significance level alpha = 0.05 for intra-cluster correlation coefficient r = 0.1, 0.15, 0.2, respectively. To compare intervention arms to the control arm, we have 3 comparisons and use conservative Bonferroni adjustment for multiple tests on significance level that alpha = 0.0167 (= 0.05/3). The sample size of 128 subject per arm may detect effect size of 0.472SD, 0.499SD and 0.524SD for r = 0.1, 0.15 and 0.2, respectively, at alpha = 0.0167. To put these numbers in perspective, using mean and SD estimated from a study of smokers in Maryland, an effect size of 0.283SD would correspond to a mean difference in salivary cotinine between the two intervention groups of 55.3 ng/mL with group SD = 195.4 ng/mL for smokers and of 0.19 ng/mL with group SD = 0.672 ng/mL for non-smokers.124 For instance a mean difference in 5 cigarettes smoked per day in the same study was 59.6 ng/mL for smokers.124 In England, following the smoke-free legislation salivary cotinine declined from mean level of 0.36 to 0.07 ng/mL (mean difference 0.29 ng/mL) among non-smokers.125 These findings support that we have sufficient power to estimate the impact of our interventions. The study is powered on an 80% retention rate, which we have achieved in other studies. Reasons for attrition will be tracked; those lost to follow up will be compared to the final sample.

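### With 16 buildings per arm, default GEE inference would run the 0.0167 tests at about 0.027; the protocol should fix building as the independent cluster and use a small-sample correction

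*Protocol article*

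**What the plan says.** The Aim Specific section applies generalized linear models with repeated measures to every aim and rests inference on GEE: "We will use the generalized estimation equation method to estimate model parameters and make statistical inference". The reason given is that GEE handles "intra- cluster (within-building or within-person) correlations". The sentence introducing these models recognises two sources of dependence: a shared building and the same participant over time. No variance estimator, reference distribution or small-sample correction is named.

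Trial design {8} describes a "cluster RCT that targets 64 randomly selected buildings (16 buildings per arm) in separate NYCHA developments". Sample Size {14} gives the cluster size for each aim: "Sampling 16 clusters (buildings) with 4 subjects per cluster (smokers for Aim 1, non-smokers for Aim 2) in each arm". It sets alpha at 0.05 for groups with versus without a treatment component. For each of the three arm-versus-control comparisons it sets 0.0167, by Bonferroni. Those levels appear only there; the statistical methods sections state none.

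Under Primary outcome, the Aim 1 model has an identity link and the Aim 2 model, for hours of exposure among non-smokers, has a log link.

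**The concern.** GEE treats its clusters as independent. In a building-allocated trial the building must therefore be the cluster. If the person is, the between-building variance drops out of the standard error of the treatment contrast. The word joining the two levels leaves the clustering unit open in the one sentence that should fix it. The Primary outcome model does not settle the matter: it indexes the building but specifies only a mean.

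With building as the cluster, a second question remains. The sandwich variance is justified by a large number of clusters. With 16 per arm its uncorrected form is biased downwards, and a normal reference ignores the uncertainty in the variance estimate. Both effects make intervals too narrow. At stake are the Bonferroni level for the three arm-versus-control contrasts and, to a lesser degree, the 0.05 level for the factorial contrasts.

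**Working it through.** **Inputs from the protocol.** K = 16 buildings per arm (Trial design {8}). From Sample Size {14}: m = 4 participants per building per aim, levels 0.0167 and 0.05, ICC 0.10, 0.15 and 0.20, and 80% retention, which leaves 4 × 0.8 = 3.2 per building.

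**Assumptions not in the protocol.** The uncorrected sandwich, the normal reference, the stated ICC applied to the change in outcome, and the variance components of the log-link simulations.

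**1. The plan's own figures.** 0.05/3 = 0.0167, as stated. For the detectable effects take SE = √(2(1+(m−1)ICC)/(Km)) and a noncentral t with 2(K−1) degrees of freedom. With m = 4 and 32 clusters per group at 0.0167 this gives 0.472, 0.499 and 0.524 SD, the published values. A normal reference would give 0.461, 0.487 and 0.512. So the 0.0167 figures were planned with a cluster-level t reference. The 0.05 figures do not discriminate as clearly. That 32 clusters are needed here, against 16 buildings per arm, is a separate matter.

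**2. Building as cluster, uncorrected sandwich, normal reference.** For a balanced identity-link contrast the sandwich variance is (K−1)/K times the unbiased one. The test therefore rejects with probability P(|t| > z√((K−1)/K)) on 2(K−1) degrees of freedom.

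| Contrast | Nominal | Cut-off | True level |
|---|---|---|---|
| 16 vs 16 | 0.0167 | 2.394 × √(15/16) = 2.318 | P(abs t30 > 2.318) = 0.0275 |
| 32 vs 32 | 0.05 | 1.960 × √(31/32) = 1.929 | P(abs t62 > 1.929) = 0.058 |

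**3. Person alone as cluster.** The true variance exceeds the estimated one by D = 1+(m−1)ICC, so the level is 2Φ(−z/√D). At nominal 0.0167:

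| ICC | D, m = 4 | Level | D, m = 3.2 | Level |
|---|---|---|---|---|
| 0.10 | 1.30 | 0.036 | 1.22 | 0.030 |
| 0.15 | 1.45 | 0.047 | 1.33 | 0.038 |
| 0.20 | 1.60 | 0.058 | 1.44 | 0.046 |

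If the ICC of the change is only 0.05, the level is 0.026 (m = 4) or 0.023 (m = 3.2).

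**4. Simulation checks.**
- 40,000 simulated trials per setting, identity link, 80% retention, ICC 0.1 to 0.2. Uncorrected building-level tests gave 0.028 to 0.029 at nominal 0.0167, family-wise 0.073 to 0.075 for three comparisons, and 0.063 to 0.064 for the factorial contrasts at 0.05.
- 1,500 full GEE fits with three visits and 64 buildings of 4. Uncorrected building-level tests gave 0.025 at 0.0167 and family-wise 0.067.

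**5. After correction.**
- Building as cluster, K/(K−1) scaling and t with 30 degrees of freedom, identity link: 0.016 to 0.018 at 0.0167, family-wise 0.043 to 0.048.
- Full GEE fits with a bias-reduced variance: 0.013 with t30 and 0.019 with z (Monte Carlo error about 0.002).
- Log link, skewed counts, two assumed sets of variance components: 0.039 and 0.054 uncorrected at 0.0167, and still 0.025 and 0.036 with K/(K−1) and t30.

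**The case against.** A reader might infer that the planned analysis over-rejects, or that it ignores the building. The protocol supports neither. It never commits to an uncorrected sandwich, a normal reference or person-only clustering. The parenthesis can fairly be read as listing two sources of correlation, both named just before it. The design is called a cluster trial, the model indexes buildings, and power was computed with building clusters, at 0.0167 with a t reference. Person-only clustering would sit badly with all of that. The exact choice of variance correction is also something that a condensed article may leave to an analysis plan that is not shown, so its absence is not an error in itself.

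A reader might also attach the 0.05 level to the arm-versus-control contrasts, where the closed form gives 0.067. In Sample Size {14} that level belongs to the 32-versus-32 comparison, where the inflation is smaller.

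These points stand, and they make the finding conditional. What survives is that the sentence fixing the method of inference leaves the independent unit loosely stated, and that the common default for the named method does not hold the level with this number of buildings.

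**Conclusion.** The point holds in conditional form. If default GEE inference is used at building level, the 0.0167 tests run at about 0.027, roughly 1.6 times nominal. The family-wise error is then about 0.07 instead of at most 0.05, and the factorial tests at 0.05 run at about 0.058 to 0.065. That is modest inflation. Clustering on person alone would be worse, at about 0.03 to 0.06 for ICC 0.1 to 0.2, but it is the less natural reading of the text.

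The figures assume the levels of Sample Size {14} carry over to the analysis, and the identity-link results assume near-normal building means. The log-link results show only the direction and possible size of the problem for Aim 2, because their variance components are assumed. This is an inexpensive improvement worth making, not a demonstrated error in the planned analysis.

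**What to change.** In the Aim Specific section, state that building is the independent cluster in every participant-level GEE, with persons and visits nested within it. Specify a bias-corrected sandwich (for example Kauermann-Carroll or Fay-Graubard) and a t reference with building-based degrees of freedom, about 30 for an arm-versus-control contrast.

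Before fixing the correction, simulate the log-link Aim 2 outcome with realistic skewness, since simple K/(K−1) scaling may not be enough there. The same simulation can show whether a stronger correction combined with t30 becomes conservative for Aim 1.

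The cost is a sentence or two, a standard software option and slightly wider intervals. In the balanced identity-link case, relative to the uncorrected interval, the arm-versus-control intervals at 0.0167 widen by about 9% (2.536/2.318 = 1.094). The factorial intervals at 0.05 widen by about 4% (1.999/1.929 = 1.036).

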### Primary outcome

1)

Self-reported average number of cigarettes smoked per day and secondhand smoking exposure (hours of secondhand smoke exposure in the building in the past 7 days) will be measured at baseline (in person interview), 3 months (phone interview) and 12 months (in person interview). Salivary cotinine will be measured for 25% of the sample at baseline and at the 12-month follow-up for smokers to evaluate reliability of self-reported smoking behavior in Aim 1 and for non-smokers to evaluate self-reported secondhand smoke exposure in Aim 2.

To examine the intervention group differences in the change of self-reported smoking (Aim 1), we will use GLMRM with identity link, E(Yijkh) = ßh + ßkhtk + ßZij, where Yijkh is an outcome variable (transformed if necessary) for smoking exposure measured at time tk (t0 = 0 for baseline; t1 = 1 for 6 months, 0 else; and t2 = 1 for 1 year, 0 else) from the ith participant of the jth building in the hth arm/group (h = 1, 2, 3, 4). For the reference group of h = 4, ßk4 = 0 for k = 0, 1, 2; so that parameter ßkh (k = 1, 2; h = 1, 2, 3 for intervention arm) indicates the difference in outcome change since baseline between intervention group h and reference group, and ß is a vector of coefficients for the vector of control variables Zij (if any). To examine if effect of treatment A depends on treatment B or vice-versa, we will test null hypothesis ßk1 = ßk2 + ßk3 for all k, which suggests independent effects of treatment A and treatment B and simpler model that E(Yijk) = ß0 + ß1A + ß2B + ßk0tk + ßk1tk A + ßk2tk B + ßZij with dummy variables A and B indicating treatment type. To examine the intervention group differences in the change in hours of secondhand smoke exposure in the building in the past 7 days for non-smokers, we will use GLMRM with log link (Aim 2). Models will be run with and without control variables (if any).

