## Data collection and management

### Plans For Assessment And Collection Of Outcomes {18a}

There are three assessments during this trial. These include a baseline assessment conducted upon recruitment and after building randomization, an interim assessment conducted over the phone approximately 3 months after the delivery of intervention, and a final long-term assessment conducted approximately 12 months after the delivery of intervention. The survey questionnaire collects information on housing conditions, indoor air quality, personal smoking behavior and cessation attempts, exposure to secondhand smoke, opinions on secondhand tobacco exposure, the smoke-free policy and tobacco policies, and health conditions. Additionally, passive drool samples from 25% of participants (n = 128) is collected at the time of the baseline assessment and at the final follow-up. Sensory building observations occur at the start of recruitment and during the final assessments to record signs of active smoking and/or tobacco/marijuana odor. The presence of cigarettes, cigars, ashtrays with/out ashes, matches or lighters will be documented within apartments and around the building premises including stairwells, elevators, hallways, laundry rooms, in/outdoor community spaces, playgrounds, and the perimeter of the buildings.

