### Secondary outcome and Sensitivity analyses

1)

We will use GLMRM with logit or log links for binary or count outcomes, respectively, to evaluate group differences in the outcome changes from baseline to 3 and 12-month follow-up. The models will include predictors of dummy variables for time and group assignment as well as for group by time interaction as described above. Aim 1 (smoking behavior) secondary outcomes are whether smokers have successfully quit (binary), the mean number of quitting attempts (continuous). Aim 2 (exposure to secondhand smoke) secondary outcomes include ever observing someone smoking indoors within the building in the past 7 days (both smoker and non-smoker participants) (binary), hours of secondhand smoke exposure in the building in the past 7 days (count), number of people smoking and number of cigarette butts in common areas of the building (count).

Differential effect of the tobacco retail environment. The impact of differential tobacco retail environments (e.g., retailer density) around each building will be systematically evaluated for the primary outcomes and for quantitative secondary outcomes listed in Aims 1 and 2. The tobacco retail environment will be measured at the longitude-latitude point coordinate of each building using a geographic kernel density estimate with standard bandwidth to estimate the square mileage density of tobacco sellers in the surrounding area for each specific building point coordinate. This information is publicly available from the City of New York. As continuous metrics, these kernel density estimates will be separated in tertiles and at median breaks and the relationships tested in Aims 1 and 2 will then be tested within separate levels of tobacco retail density. We will also extend the GLMRM with identity or log link for each outcome variable in Aims 1 and 2 by adding the factor for retail environment, its interaction with group, time, and group by time interaction. In addition to the analysis for effect of a pre-specified modifier (the retail environment), we will conduct several a priori subgroup analyses to explore potential differential effect of the interventions in the continuous outcomes by age, sex, knowledge, and attitude towards the policy.

We will evaluate reliability of self-reported measures of active and passive smoking and revisit the primary analyses adjusting for potential imperfect reliability using regression calibration approaches.

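### The displayed Aim 1 primary model omits the common time effect, so as printed its coefficients are within-arm changes, not the stated differences from control

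*Protocol article*

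**What the plan says.** In the protocol article, section Primary outcome, the Aim 1 comparison is a repeated-measures linear model fitted by generalized estimating equations, displayed as "E(Yijkh) = ßh + ßkhtk + ßZij". Time is coded by visit indicators: "t0 = 0 for baseline; t1 = 1 for 6 months, 0 else; and t2 = 1 for 1 year, 0 else". Arm 4, the standard approach, is the reference: "For the reference group of h = 4, ßk4 = 0 for k = 0, 1, 2; so that parameter ßkh" (for the three intervention arms at the two follow-ups) "indicates the difference in outcome change since baseline between intervention group h and reference group".

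The same section gives a simpler model, for use if the two treatments act independently: "E(Yijk) = ß0 + ß1A + ß2B + ßk0tk + ßk1tk A + ßk2tk B + ßZij". Here A and B are treatment indicators.

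The next section, Secondary outcome and Sensitivity analyses, says: "The models will include predictors of dummy variables for time and group assignment as well as for group by time interaction as described above".

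For Aim 2 the article names a log-link model and prints no equation. The interim visit is described under Plans For Assessment And Collection Of Outcomes {18a} as "an interim assessment conducted over the phone approximately 3 months after the delivery of intervention".

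**The concern.** In a model with arm intercepts and arm-by-time coefficients, setting the reference arm's time coefficients to zero is ordinary reference coding only if a time main effect is also present. Without one, the zeros are a substantive restriction: the control mean may not move after baseline.

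What is at stake is the controlled comparison itself. Coded literally, the model gives three uncontrolled pre-post estimates. Any background change in smoking, regression to the mean or drift in self-report would count as intervention effect in all three arms. The article itself gives reasons to expect movement in the control arm. Under Explanation For The Choice Of Comparators {6b}, control buildings are sites where the housing authority concentrates its own smoke-free programming. Under Eligibility Criteria {10}, the policy was modified during recruitment.

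**Working it through.** The plan states no figure to reproduce here. The check is algebra, followed by an illustration of size.

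**Step 1. Arm means under the printed model (covariates held fixed).**

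| | Baseline | Follow-up k (k = 1, 2) | Change |
|---|---|---|---|
| Control (h = 4) | ß4 | ß4 + 0 | 0, by constraint |
| Arm h = 1, 2, 3 | ßh | ßh + ßkh | ßkh |

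So ßkh is arm h's own change. It equals the difference from control only if the true control change is zero. The k = 0 part of the constraint does nothing, because t0 = 0.

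**Step 2. Parameter count.** Four arms at three visits give 12 means. The printed model has 4 intercepts + 3 × 2 time coefficients = 10 parameters. The two missing ones are the control arm's changes at the two follow-ups. Adding ßk0 for k = 1, 2 gives 12 parameters. Control change is then ßk0, arm h's change is ßk0 + ßkh, and the difference is ßkh, as the article says.

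**Step 3. Nesting.** The additive model gives control (A = B = 0) a change of ßk0, which is free. The printed full model fixes that change at zero. The additive model therefore allows means that the full model forbids, so it is not a special case of it. With ßk0tk restored to the full model, the additive model is nested in it.

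**Step 4. Bias.** If control changes by c and arm h by c + d, the printed model estimates c + d instead of d. The bias is c, whatever the SD or correlation.

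**Step 5. Illustrative false-positive rate (d = 0).**
- From Sample Size {14}: 16 buildings × 4 smokers = 64 per arm; ICC 0.1, the lowest of the three values given.
- Assumed, not in the document: within-person correlation 0.6 and a shared fall of 0.2 SD. Applying the planning ICC to the change score is also an assumption.
- Design effect = 1 + (4 − 1) × 0.1 = 1.3.
- SE of a within-arm change = √(2 × (1 − 0.6) × 1.3 / 64) = √0.01625 = 0.127 SD.
- Standardised shift = 0.2 / 0.1275 = 1.57. Two-sided rejection at 0.05 ≈ Φ(1.57 − 1.96) = Φ(−0.39) ≈ 35%. At 0.0167 it is about 20%.

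| Within-person correlation | SE (SD units) | Shared fall (SD) | Rejection at 0.05 |
|---|---|---|---|
| 0.6 | 0.127 | 0.1 | 12% |
| 0.6 | 0.127 | 0.2 | 35% |
| 0.6 | 0.127 | 0.3 | 65% |
| 0.4 | 0.156 | 0.2 | 25% |
| 0.8 | 0.090 | 0.2 | 60% |

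With the article's 80% retention (64 × 0.8 = 51.2 per arm) and the same design effect, the 0.6 correlation and 0.2 SD case gives about 29%.

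**Step 6. Simulation.** Both models were fitted by GEE clustered on building to 300 simulated trials per scenario, with no treatment effect. Assumptions: SD 8 cigarettes per day, baseline mean 12, within-person correlation 0.5, ICC 0.1. Results are for arm 1 at 12 months.

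| Shared change (cigarettes/day) | Printed model: mean estimate | Rejected | With ßk0tk: mean estimate | Rejected |
|---|---|---|---|---|
| 0 | 0.12 | 9% | 0.19 | 6% |
| −1 | −1.19 | 26% | −0.17 | 7% |
| −2 | −1.95 | 55% | 0.04 | 7% |
| −3 | −2.98 | 85% | 0.05 | 6% |

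In one further data set (shared change −2, true effect −1), the printed model returned −4.43. That is exactly arm 1's observed change; the observed difference from control was −1.45.

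**The case against.** The strongest reply is that the intended model can be recovered from the surrounding text. The stated meaning of ßkh is a difference in change from control. The additive model carries ßk0tk. The secondary-outcome section lists time, group and group-by-time terms and says they are as described above, which points back to this very model. Nothing in the prose says that controls are expected not to change.

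Most of this stands. A reader might infer from the equation that the investigators deliberately assume a flat control arm, and the rest of the text does not support that. The harm is therefore conditional: it arises only if the displayed equation is coded as it stands. But the other statements do not correct the equation. They make the section inconsistent with itself, and this is the only displayed model that compares the four arms for Aim 1.

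Four further limits are fair:
- The false-positive rates depend on assumed correlations and trends. Only the bias is free of them.
- The printed model's standard error, smaller by a factor of 1/√2 = 0.71 than that for a difference between two arms, is not a separate fault. It restates the missing control contrast.
- The label "t1 = 1 for 6 months, 0 else" disagrees with the 3-month visit used elsewhere, but t1 is a 0/1 indicator for the only interim visit, so no estimate changes.
- The fault should not be read into the other models. The secondary-outcome text already names the right terms, and no Aim 2 equation is printed that could be shown to lack one.

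**Conclusion.** The equation is wrong as written and needs correcting. It estimates each arm's own change since baseline, while the same sentence claims a difference from control. It also does not contain the additive model that is presented as its simplification. The most likely explanation is a dropped time main effect. That part is a judgement; the algebra is not.

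If the equation were implemented literally, the bias in every intervention effect would equal the control arm's true change. For a shared 0.2 SD fall, with 64 per arm and a design effect of 1.3, false positives per arm at alpha 0.05 would be about 35% at a within-person correlation of 0.6, and 25% to 60% for correlations from 0.4 to 0.8. These rates illustrate literal coding and do not predict what this trial will report.

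**What to change.** Write the Aim 1 model as E(Yijkh) = ßh + ßk0tk + ßkhtk + ßZij, with ßk4 = 0 for k = 1, 2. Then ßkh is the difference in change from the reference group, as the text intends, and the additive model becomes a proper reduction.

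State in one sentence that the Aim 2 log-link model uses the same time, group and group-by-time structure. The secondary-outcome text can stay as it is, since its back-reference will then be correct. As a minor label correction, define t1 as the 3-month assessment.

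The cost is a text edit and two more parameters. No data collection, sample size or visit schedule changes.

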### Objectives {7}

The broad objective of this study is to use an experimental design to test two smoke-free policy compliance support interventions: (A) a “compliance through reduction (via relocation and reduction in personal smoking) and cessation” intervention targets households with smokers and involves support to shift smoking practices to designated areas and reducing personal smoking, and deliver in-residence smoking cessation support services via trained peer educators and (B) a “compliance through resident endorsement” intervention involving voluntary adoption of smoke-free living environments through personal pledges, visible door markers and/or via social media. We will compare randomly sampled participants in buildings that receive A or B or A plus B to the NYCHA standard approach.

We seek to achieve the following specific aims:

Aim 1: Experimentally test if compliance support interventions reduce personal smoking behavior.

Aim 2: Experimentally test if compliance support interventions reduce secondhand smoke exposure.

Aim 3: Determine if the tobacco retail environment surrounding each building moderates the relationship between compliance support interventions and smoking-related outcomes.

We hypothesize that the reduction/cessation plus resident endorsement intervention will yield significantly larger reductions in personal smoking and second-hand smoke exposure, compared to standalone interventions and the standard approach.

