#### Arm 1: Reduction (via relocation and reduction in personal smoking)/Cessation

The reduction/cessation arm (Arm 1) “meets smokers where they are” using a) a harm reduction approach that reinforces the use of designated smoking areas available and/or identifies ways residents can reduce their personal smoking more generally via motivational interviewing skills thereby encouraging compliance via relocation and personal smoking reduction; along with b) in-residence cessation support to reduce barriers to participation in cessation services. Enrolled participants who are smokers will be referred by the survey team to peer educators from Health People. The peer educator will coordinate smoking cessation support, including serving as a liaison between participant and research team, providing information regarding the smoke-free policy and opportunities for relocation, and connecting participant to tobacco replacement therapy and/or physician support if deemed appropriate.

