#### Arm 2: Resident Endorsement

The resident endorsement model (Arm 2) seeks to engage residents by using an empowerment/network-based approach to shift the culture of health in buildings that encourages residents to collectively tackle indoor smoking and secondhand smoke exposure via physical demarcations and/or social media. Buildings assigned to this arm will be targeted for a series of 2 in-residence programs that involve community forums and the creative arts to garner resident endorsements of smoke-free living environments. Premised on resident engagement, this arm seeks to impact social and physical dimensions of the residential environment to achieve compliance. The sessions will: 1) inform residents of risks associated with smoking and secondhand smoke; 2) identify reasons to have a smoke-free home, 3) ask residents to sign a pledge on paper and/or virtually; 4) display smoke-free signage on doors and/or social media pages with an original hashtag (#Smokefree[building address]); and 5) refer residents to the Smoke-free NYCHA website for information on the policy and existing cessation resources.

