#### Arm 3: Combined Intervention

There will be buildings assigned to receive both models (Arm 3) for which in-residence programs based on the resident endorsement treatment and the smoking reduction/cessation treatment will be provided. Both will occur simultaneously with one geared toward all building residents (resident endorsement) and the other targeting smokers (smoking reduction/cessation) with the goal of reducing both personal smoking and secondhand smoke exposure.

The interventions and comparison group are outlined in Table 1.

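### The null hypothesis for the A-by-B interaction has the arm subscripts in the wrong places, so it tests twice the effect of B plus the interaction, not the interaction

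*Protocol article*

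**What the plan says.** Objectives {7} defines treatment A as "A) a “compliance through reduction (via relocation and reduction in personal smoking) and cessation” intervention" and treatment B as "B) a “compliance through resident endorsement” intervention". Trial design {8} numbers the arms "1) reduction/cessation, (2) resident endorsement, (3) reduction/cessation plus resident endorsement and (4) the standard approach". The intervention descriptions keep that order: "The reduction/cessation arm (Arm 1", "The resident endorsement model (Arm 2" and, for the combination, "There will be buildings assigned to receive both models (Arm 3". The comparator is labelled Arm 4 in the section on choice of comparators {6b}.

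The Primary outcome section indexes arms by h = 1 to 4 and takes h = 4 as reference. It defines ßkh as the difference between arm h and the reference in change since baseline at follow-up k. To see whether the effect of one treatment depends on the other, the plan will "test null hypothesis ßk1 = ßk2 + ßk3 for all k". That null is described as one "which suggests independent effects of treatment A and treatment B and simpler model". The simpler model has A-by-time and B-by-time terms and no A-by-B term.

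**The concern.** Under this numbering, the printed equation sets the effect of A alone equal to the effect of B alone plus the effect of the combination. That is not independence of the two treatments. Rearranged, it says ßk3 = ßk1 - ßk2: if B helps, adding B to A gives a worse result than A alone. This is the opposite of the hypothesis in Objectives {7}, that the combination does better than either intervention alone.

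The test decides whether the Aim 1 primary outcome is read from the four-arm model or from the additive factorial model. A wrong contrast can err in two ways. It can give up the factorial model when that model is correct. It can also keep the factorial model when A and B cancel each other, so that the main effects mislead.

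**Working it through.** **Inputs.** Arm numbering, reference arm and meaning of ßkh: as set out above. Design figures from Sample Size {14}: 16 buildings per arm, 4 participants of one smoking status per building, ICC r = 0.1 to 0.2, two-sided alpha 0.05, effect sizes 0.283 SD and 0.472 SD. Effects of 0.4 and 0.2 SD are assumptions added for illustration.

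**Step 1: what each null says.** Let a and b be the effects of A and B on change versus arm 4 (positive = benefit), and g the interaction. Then:

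- ßk1 = a, ßk2 = b, ßk3 = a + b + g
- correct contrast: ßk3 - ßk1 - ßk2 = g
- printed contrast: ßk1 - ßk2 - ßk3 = a - b - (a + b + g) = -(2b + g)

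The printed contrast is a pure test of B when g = 0, has the same size as the interaction when b = 0, and otherwise mixes the two.

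**Step 2: check against the plan's own simpler model.** There, the difference from control in change at time k is the A-by-time coefficient in arm 1, the B-by-time coefficient in arm 2, and their sum in arm 3. The model thus forces ßk3 = ßk1 + ßk2 and does not reproduce the printed null. The printed null would be right only if arm 1 were the combined arm, and no section numbers the arms that way.

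**Step 3: standard error.** In terms of arm means, both contrasts add and subtract all four arms with weight 1, so they have the same variance. Per arm the variance is (1 + 3r)/64 in SD² units.

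- r = 0.1: SE = sqrt(4 × 1.3/64) = 0.285 SD
- r = 0.2: SE = sqrt(4 × 1.6/64) = 0.316 SD

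**Step 4: rejection probability** (normal approximation, one time point, full retention). For a contrast of size c it is about Φ(|c|/SE - 1.96), plus the opposite tail. For example, b = 0.4 and g = 0 give c = 0.8, 0.8/0.285 = 2.81, and Φ(0.85) = 80%.

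| r | b | g | 2b + g | Printed test rejects | Correct test rejects |
|---|---|---|---|---|---|
| 0.1 | 0.2 | 0 | 0.4 | 29% | 5% |
| 0.1 | 0.283 | 0 | 0.566 | 51% | 5% |
| 0.1 | 0.4 | 0 | 0.8 | 80% | 5% |
| 0.1 | 0.472 | 0 | 0.944 | 91% | 5% |
| 0.2 | 0.283 | 0 | 0.566 | 43% | 5% |
| 0.2 | 0.472 | 0 | 0.944 | 85% | 5% |
| 0.1 | 0.4 | -0.8 | 0 | 5% | 80% |
| 0.1 | 0.472 | -0.944 | 0 | 5% | 91% |
| 0.1 | 0 | 0.5 | 0.5 | 42% | 42% |

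Simulating 20,000 trials per scenario at r = 0.1 gave 50% (b = 0.283) and 90% (b = 0.472) rejection by the printed test with g = 0. At b = 0.472 and g = -0.944 it gave 5% for the printed test against 90% for the correct one.

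**Step 5: what the additive model would report under antagonism.** With balanced arms, its effect of A is the average of a (without B) and a + g (with B), which is a + g/2. With a = b = 0.4 and g = -0.8 this is 0.4 - 0.4 = 0, and the same holds for B. Both treatments would appear to do nothing although each works alone.

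**Step 6: power of the correct test.** At r = 0.1, 80% power needs g = (1.96 + 0.84) × 0.285 = 0.80 SD.

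**The case against.** The strongest reply is that this is a slip of subscripts with the intent stated alongside. The sentence gives the purpose, and the simpler model is written out. An analyst who compares the four-arm model with that additive model would run the correct test, so harm arises only if the contrast is coded literally. That is fair, but the literal contrast is the hypothesis as specified, and nothing in the article points the programmer to another.

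Second, when additivity holds and the printed test falsely rejects, the four-arm model that remains is still unbiased. The loss is precision, not validity. This stands.

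Third, the damaging case needs antagonism, whereas the investigators expect the combination to do best. If B works and the interaction is synergistic, 2b and g have the same sign, and the printed test keeps the four-arm model more readily. This also stands, but the risk is wider than the exact point g = -2b. For b > 0, |2b + g| is smaller than |g| whenever g < -b. The printed test therefore loses sensitivity whenever adding B makes A do worse than it does alone, which is when a pooled main effect misleads most.

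Fourth, Sample Size {14} already plans three comparisons of intervention arms with control, and the article does not say they are dropped if the simpler model is adopted. That is correct, so on this point only a clarifying statement is needed.

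Finally, the rejection rates are illustrative. The plan tests both follow-ups jointly and allows for 80% retention, and the calculation treats the ICC and SD as those of the change. At 3.2 participants per building and r = 0.1, SE = sqrt(4 × 1.22/51.2) = 0.309, and the 80% at b = 0.4 becomes Φ(0.8/0.309 - 1.96) = 74%. The size moves; the conclusion does not.

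**Conclusion.** The point holds: the printed null is wrong under the article's only arm numbering, and it contradicts the model it is meant to support. This is algebra and rests on no assumption about effect sizes. Wrong model choice is a risk when B has an effect, not a certainty in every data set; if b = 0 the two tests have the same power. Within the table's assumptions, false rejection of additivity runs from 29% to 91% depending on b and the ICC. An antagonistic interaction of -2b is rejected only 5% of the time, against 80% to 91% for the correct test at the sizes shown. The error sits in the model-selection step for a primary outcome of a factorial trial, so it must be corrected before analysis.

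**What to change.** In the Primary outcome section, replace the null with ßk3 = ßk1 + ßk2 for k = 1, 2 (equivalently, all A-by-B-by-time terms are zero). State beside the model that h = 1, 2, 3, 4 are A, B, A+B and standard approach. Carry the same contrast into the analysis plan and code.

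Add that the four-arm contrasts are reported whatever the test shows. Because the correct test reaches 80% power only near an interaction of 0.8 SD, its non-significance alone should not license the additive model. The cost is one line of text and one contrast statement; no design or data collection changes.
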